### Data management

2.7

Data collection is the responsibility of the clinical trial staff under the supervision of the principal investigator. The principal investigator is responsible for ensuring the accuracy, completeness, legibility and timeliness of the data reported. Case report forms in a paper format will be used for this study. Forms will be reviewed against source documentations. Any changes or corrections will be tracked on paper. The investigator will permit inspections of the trial site and documentation by clinical research personnel, as well as external auditors or representatives from regulatory authorities.

Subject privacy and confidentiality will be strictly held in trust by the principal investigator and trial personnel. This includes the study protocol, documentation, data and all other information generated. A unique number will be assigned to each subject at the start of the trial and this, with the subject's initials, may be used to identify the subject. The investigator will keep a list of identification codes or initials used for each subject along with the unique number assigned. IRB representatives, or other regulatory bodies may inspect all documents and records required to be maintained by the investigator.

### Data analysis

2.8

As a pilot study, sample size calculations were not performed; a sample size of 15 patients per treatment group was selected to provide sufficient preliminary data on treatment safety, tolerability and efficacy in onychomycosis patients.

The per‐protocol and intention‐to‐treat populations will be included for safety and efficacy analyses. Descriptive statistics will be conducted for subject demographic and baseline parameters including sex, Fitzpatrick skin type (I‐VI) and fungal species. All AEs will be presented by description, category, frequency, severity and causality; differences in incidence between Groups A and C will be tabulated. Statistical analyses will be performed if there are sufficient data points available.

Statistical analyses for the difference in proportion of subjects achieving a pre‐specified efficacy endpoint between treatment groups will be conducted using the Chi‐square test; *p* < 0.05 will be considered statistically significant. Nail measurements will be converted to the mean increase in clear nail, both in terms of clear nail length from the proximal nail fold and clear nail surface area. The mean increase in clear nail, mean increase in clear nail as a function of the number of treatments and energy dose administered, mean increase in clear nail as a function of the number of visits attended and mean pain scores at treatment visits will be analysed using ANOVA or the Kruskal–Wallis test depending on data distribution; *p* < 0.05 will be considered statistically significant. Additional correction measures will be performed at the statistician's discretion.

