### Study intervention

2.2

On day 0, patients will be randomized (1:1:1) to one of three treatment groups (Groups A–C) based on a computer‐generated randomisation schedule generated prior to the start of the study (Figure 1). Group A will undergo nine treatment sessions, which includes the first session at day zero followed by four weekly sessions then four monthly sessions. Group B will undergo 7 treatment sessions, which includes the first session at day 0 followed by sessions every 2 weeks for 2 sessions then 4 monthly sessions. Group C will undergo 12 treatment sessions, which includes the first session at day 0 followed by sessions every 2 weeks.

Non‐responders at the end of the month 6 visit (day 168) or month 9 visit (day 252) as judged by the US FDA recommended endpoint (i.e., “temporary increase of clear nail”) will be given the option to undergo retreatment once per month for 3 months up to month 9 or month 12, respectively (Figure 1).^13^ Subjects who do not wish to undergo retreatment will be asked to return for month 9 and month 12 visits.

Tinea pedis is a common co‐infection seen in onychomycosis patients^17^; in this study, patients presenting with concomitant tinea pedis, at the investigator's discretion, may be provided with topical antifungal agents for treating affected skin areas. Toenails will be strictly avoided. No local anaesthetic, petroleum jelly nor metallic‐based topical treatments (e.g., aluminium chloride, silver nitrate) are to be used in the toenail areas during this study. Concomitant use of oral antifungal agents is not permitted.

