### Study assessments

2.4

All enroled subjects will be assessed until month 12 for the evaluation of efficacy and safety endpoints, including interim treatment visits (Figure 1). Clinical response will be evaluated based on in‐person assessments and photographic images of the treated hallux, both in terms of the affected nail area and nail length. Mycology testing will be performed at baseline, day 84 (month 3), day 168 (month 6), day 252 (month 9) and day 336 (month 12).

Incidence of adverse events (AEs) will be recorded throughout the entire study period; each AE will be graded based on severity (mild, moderate, severe) and relatedness to the study intervention. The investigator will deem an AE as ‘expected’ if it's consistent with previous reports in the literature,^10^, ^11^, ^18^ which includes local application site reactions such as pain, bruising, heat sensitivity and tingling. Burns, blisters, or nail disfigurement will be considered as ‘unexpected’ AEs. Any new clinically relevant findings deemed by the investigator will be reported as an AE. Patients will be asked to report their pain level—categorised as none, mild, moderate or severe—before treatment, during treatment, and 10‐min post‐treatment. Additionally, patient‐reported outcomes (PROs) will be recorded at pre‐specified timepoints of which patients will be asked to rate (a) how their daily activities are affected, (b) how their lifestyle activities (e.g. sports, hobbies) are affected and (c) how their mood is affected.

Subjects who wish to discontinue from treatment will be asked to complete all remaining study assessments as planned. The principal investigator may withdraw a subject from the study if there is significant protocol non‐compliance, AEs or other medical conditions such that the continued study participation would not be in the interest of the subject, or subject meeting the exclusion criteria during the study period. If a subject fails to return for 2 scheduled visits, and is unable to be contacted (through multiple telephone calls and letters), the site staff will make a reasonable effort to ascertain reason(s).

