### Primary endpoints

2.5

The co‐primary endpoints include (a) an acceptable safety and tolerability profile at the end of month 6 (day 168 ± 7 days) defined by treatment adherence with minimal mild‐to‐moderate treatment‐related AEs (expressed as frequencies per category), which resolve before further treatments with no sequelae, and (b) proportion of subjects achieving the following endpoints at month 3 (day 84 ± 7 days) and month 6 (day 168 ± 7 days): month 3—US FDA definition of ‘temporary increase in clear nail’ with evidence of nail improvements defined as an increase in clear nail measured in distance from the proximal nail fold or an increase of the clear nail area; month 6—achieving either (1) ≥ 6 mm increase in clear nail measured in distance from the proximal nail fold, (2) an additional 60 mm^2^ of the treated nail area achieving clearance with evidence of outward growth or (3) complete clearance if less than 6 mm of the distal nail was involved at baseline.

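### As written, the adverse-event comparison names Groups A and C but not B, and per-protocol has equal standing with intention-to-treat for a safety endpoint partly defined by adherence

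*Protocol article*

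**What the plan says.** All references are to the protocol article.

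- **Arms (Study intervention, 2.2).** Patients are randomised 1:1:1 "to one of three treatment groups (Groups A–C"). "Group A will undergo nine treatment sessions" and "Group B will undergo 7 treatment sessions"; Group C has 12.
- **AE analysis (Data analysis, 2.8).** "All AEs will be presented by description, category, frequency, severity and causality". The sentence goes on to say that "differences in incidence between Groups A and C will be tabulated". It gives no reason for naming two groups. Efficacy proportions, in the same section, are compared between treatment groups without any restriction.
- **Populations (2.8).** The per-protocol and intention-to-treat "populations will be included for safety and efficacy analyses". Neither is given precedence for safety.
- **Co-primary safety endpoint (Primary endpoints, 2.5).** An acceptable safety and tolerability profile at month 6 is "defined by treatment adherence with minimal" mild-to-moderate related AEs.
- **Withdrawal (Study assessments, 2.4).** The principal investigator "may withdraw a subject from the study if there is significant protocol" non-compliance; AEs are listed beside it as a ground. Patients who choose to stop treatment are asked to stay for the remaining assessments.
- **Objective (Methods/Design, 2).** The secondary objective is to find the best dosing frequency, if there is one, for a pivotal trial.

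**The concern.** There are two separate issues in the same short section.

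First, choosing a regimen means weighing efficacy against tolerability in each of three arms. As worded, efficacy is compared across three arms and AE incidence across two. The arm without a stated AE comparison has the fewest planned sessions, so it is the natural low-exposure reference.

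Second, adherence is part of the safety outcome. A per-protocol set is commonly built on adherence or completion. If this one is, the per-protocol version of the co-primary safety result is partly fixed by who is allowed into it. Giving that result the same standing as intention-to-treat leaves open which of two possibly different answers decides whether the profile is acceptable.

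**Working it through.** **Inputs.** 15 patients per group (2.8); 45 planned in total (2); 39 enrolled (Trial status, 4); session schedules (2.2).

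**Reproducing the plan's figures.**
- Total: 3 × 15 = 45, as stated. The article says no sample size calculation was done, so there is no power figure to check.
- Sessions: A = 1 + 4 + 4 = 9; B = 1 + 2 + 4 = 7; C = 12. The counts for A and B agree with the text, and C's 12 is stated directly.

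**What the A-and-C wording leaves out.**
- Planned patients in the AE comparison: 30 of 45, so 15/45 = 33% are outside it.
- On the 39 enrolled, if the arms are balanced (an assumption, as arm sizes are not reported): 39/3 = 13 per arm, so 26 of 39 are compared.
- Planned sessions covered, all three arms: 7 to 12, a span of 5 and a ratio of 12/7 = 1.71.
- Planned sessions covered, A and C only: 9 to 12, a span of 3 and a ratio of 12/9 = 1.33.
- Structure of the regimens: A and B both end with four monthly sessions and differ in the early phase (five weekly against three two-weekly). B and C share three two-weekly sessions at the start and differ afterwards. A against C changes both phases at once, so without B an AE difference could not be traced to early intensity or to later frequency.

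**Per-protocol safety.** The article does not define the set and gives no discontinuation rate, so nothing can be computed from it. The following only shows how sensitive small arms are, on assumed figures. Let *n* be the arm size, *a* the patients with a treatment-related AE, and *k* the number of those excluded from the per-protocol set. The intention-to-treat rate is *a/n* and the per-protocol rate is (*a* − *k*)/(*n* − *k*). With *a* = 3:

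| *k* excluded | *n* = 15 | *n* = 13 |
|---|---|---|
| 0 | 3/15 = 20.0% | 3/13 = 23.1% |
| 1 | 2/14 = 14.3% | 2/12 = 16.7% |
| 2 | 1/13 = 7.7% | 1/11 = 9.1% |
| 3 | 0/12 = 0% | 0/10 = 0% |

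The *k* = 0 row matters as much as the others: if the per-protocol rule excludes nobody with an AE, the two populations give the same rate.

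For the adherence component, suppose 4 of 39 stopped and the rule required completion (both assumed). Adherence would be 35/39 = 89.7% in all treated patients and 35/35 = 100% per protocol.

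**The case against.** On Group B, the likeliest explanation is a slip. The arms are written elsewhere as a range with a dash, and the efficacy comparison leaves no arm out. A reader might infer that Group B's patients drop out of the safety data. The article does not support that: AEs are recorded throughout for everyone, and all of them are to be presented by frequency, severity and causality. What is affected is a tabulation of differences, with tests only if the data suffice. Pain by number and frequency of treatments (Secondary endpoints, 2.6) is not limited to A and C either. All of this stands and reduces the weight of the point. It does not make the sentence right, since someone following it literally would produce a two-arm comparison.

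On the per-protocol set, a reader might infer that it removes patients who could not tolerate treatment, so that their AEs vanish. The article does not say so. Four things stand against that reading:
- The set is undefined here, and the definition may properly sit in the full protocol or analysis plan.
- Treatment procedures (2.3) allows power and time settings to be adjusted for tolerability, so poor tolerance need not be a deviation.
- Patients who stop treatment are asked to remain under assessment.
- Intention-to-treat is also used for safety. Randomisation and the first session are both on day 0, so that set should nearly coincide with all treated patients. Any AE case lost from the per-protocol result would still appear there.

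What survives is narrower: the article gives the two sets equal standing for an endpoint that includes adherence.

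**Conclusion.** The point holds in a limited form.

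- **Group B.** This rests on the text itself. One of three randomised arms, 15 of 45 planned patients, has no stated between-group AE comparison. Its AEs are still presented, and the cause is probably wording. It deserves correction because safety is co-primary and the trial is meant to inform a choice among all three regimens.
- **Per-protocol safety.** The equal standing of the two populations is stated. The harm is conditional: it arises if the per-protocol rule depends on adherence or completion. Its size is unknown, and the percentages above illustrate assumed counts and do not estimate an effect.

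The 13-per-arm figure assumes balanced arms. Neither part threatens the trial's data or conduct.

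**What to change.** 1. Reword the AE sentence so that differences in incidence are tabulated between Groups A, B and C.
2. State that the co-primary and all other safety analyses use every randomised patient who received at least one session, grouped as randomised, and that any per-protocol safety result is supportive only.

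Grouping as randomised is preferable to grouping by regimen received. The arms use the same device and differ only in the number and timing of sessions. A patient who stops early has received none of the three regimens as planned, and regrouping could sort patients by tolerance.

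The cost is two sentences, with no new data and no change to treatment or visits. The tolerability figure that leads may be slightly less favourable than a per-protocol one.

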### Study participants

2.1

Adult patients presenting with DSO of one hallux, with 20%–75% involvements of the nail area, nail thickness of ≤3 mm and no area of infection <3 mm from the proximal nail fold, will be enroled and allocated to treatment. Inclusion and exclusion criteria are summarised in Table 1. No eligibility waivers will be permitted.

**TABLE 1 ski2455-tbl-0001:** Patient eligibility criteria.

Inclusion criteria
Provide written informed consent Aged ≥18 years Not pregnant or breastfeeding Subject presenting with distal subungual onychomycosis of one hallux Mycology‐positive diagnosis confirmed by the detection of a dermatophyte One hallux as a treatment target with 20%–75% nail area affected One hallux as a treatment target with a thickness of ≤3 mm No area of infection <3 mm from the proximal nail fold No more than 4 toenails showing visual signs of onychomycosis including the treatment target Subject agrees not to take any oral or topical antifungal treatments for the duration of the study Subject able to undergo study assessments

Exclusion criteria

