Patients will be evaluated at enrolment, which includes medical history, concomitant medications (prescriptions, over‐the‐counter medications, supplements), onychomycosis disease duration and treatment history, and toenail measurements (i.e. nail thickness, total affected nail surface area and lowest distance between the affected nail area to the proximal nail fold) (Figure 1); Flyers/posters, online and radio advertisements will be used to increase enrolment. Once a patient provides written informed consent and meets the eligibility criteria, one affected hallux will be sampled for mycology testing (i.e., fungal culture, polymerase chain reaction [PCR] and direct potassium hydroxide [KOH] microscopy). Patients testing PCR and/or fungal culture positive for dermatophytes will be eligible to join the study.

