## TRIAL STATUS

4

Initial IRB approval of the study protocol was obtained in December 2022 and enrolment began in March 2023. Study inclusion criteria was expanded from ‘20%–50% nail area affected’, and ‘nail thickness ≤1.5 mm’ to ‘20%–75% nail area affected’ and ‘nail thickness ≤3.0 mm’, which were covered in the first protocol amendment to increase the recruitment rate. Mycology testing at enrolment was revised to include PCR testing allowing for a positive dermatophyte detection by PCR and/or fungal culture. The revised protocol received IRB approval in June 2023. Enrolment began in March 2023 and is complete as of May 2024. A total of 39 patients were enroled due to difficulty in confirming a positive dermatophyte infection. Study visits will continue through 2024, with interim data available in December 2024 and anticipated trial completion by May 2025.

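### Clear-nail gain is compared between regimens without the baseline extent already on record: valid, but possibly less precise than it need be with about 13 patients per arm

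*Protocol article*

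**What the plan says.** Section 2.8 (Data analysis) defines the continuous efficacy outcome: "Nail measurements will be converted to the mean increase in clear nail, both in terms of clear nail length from the proximal nail fold", with clear nail surface area as its companion. This mean increase "will be analysed using ANOVA or the Kruskal–Wallis test depending on data distribution", at the 5% level. No covariate is named. A closing sentence leaves further corrections to the statistician without saying what they might be.

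Section 2.1 (Study participants) lists the toenail measurements taken at enrolment: "nail thickness, total affected nail surface area and lowest distance between the affected nail area to the proximal nail fold". Table 1 sets the eligible extent: "One hallux as a treatment target with 20%–75% nail area affected". Section 4 (Trial status) says this range was widened from 20–50% by changes "which were covered in the first protocol amendment to increase the recruitment rate", and that 39 patients were enrolled against the 45 planned.

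Section 2.5 (Primary endpoints) acknowledges that baseline extent limits the achievable gain. It gives small lesions their own month-6 criterion: "complete clearance if less than 6 mm of the distal nail was involved at baseline".

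**The concern.** A nail cannot gain more clear area than was affected at the start. With eligibility from 20% to 75%, the largest possible area gain differs 3.75-fold between patients (75/20). If actual gains follow that ceiling even loosely, part of the spread in gain within each arm reflects where patients started and not what the regimen did. ANOVA leaves that part in the error term, and Kruskal–Wallis has no baseline term either. At about 13 per arm, any avoidable noise weakens the comparison that bears on the secondary objective of finding a dosing frequency. The variable that could remove it is already recorded.

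**Working it through.** **Inputs from the article.** Three arms, 1:1:1; planned 45/3 = 15 per arm; enrolled 39/3 = 13 per arm (equal arms assumed); 5% level; extent 20–75%, formerly 20–50%. The article gives no SD, effect size, power or baseline–gain correlation (ρ), and no sample size calculation, so there is no figure of its own to reproduce. Everything below that needs ρ or a cleared fraction is an assumption shown over a range.

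**Step 1: precision as a function of ρ.** Adjustment multiplies the error variance by (1 − ρ²). Estimating the slope with chance imbalance multiplies it by about 1 + 1/34 = 1.029, and residual degrees of freedom fall from 36 to 35. The equivalent unadjusted size is 13 / [(1 − ρ²) × 1.029]. Omnibus power is from the noncentral F with one arm 1 SD from the other two (f = √(2/9) = 0.471).

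| Analysis | Omnibus power | Equivalent n per arm | Pairwise difference detectable with 80% power (SD) |
|---|---|---|---|
| Unadjusted | 0.716 | 13 | 1.13 |
| Adjusted, ρ = 0 | 0.70 | 12.6 | 1.15 |
| Adjusted, ρ = 0.2 | 0.72 | 13.2 | 1.12 |
| Adjusted, ρ = 0.4 | 0.78 | 15.0 | 1.05 |
| Adjusted, ρ = 0.5 | 0.83 | 16.8 | 0.99 |
| Adjusted, ρ = 0.6 | 0.88 | 19.7 | 0.92 |

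Break-even is ρ = √(1 − 1/1.029) ≈ 0.17. At ρ = 0.4, adjusting 39 patients gives the precision of the planned 45 unadjusted.

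**Step 2: what ρ might be, for area.**

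*Model A: gain = affected area × an independent cleared fraction.* Let the area have mean M and variance V, and the fraction mean m and variance s². Then R² = m²V / [m²V + s²(V + M²)]. For extent uniform on 20–75%, M = 47.5 and V = 55²/12 = 252.1 (SD 15.9).
- Fraction uniform on 0–0.6 (m = 0.3, s² = 0.03): R² = 22.7/(22.7 + 75.2) = 0.23, ρ = 0.48.
- Fraction uniform on 0.1–0.9 (m = 0.5, s² = 0.0533): R² = 63.0/(63.0 + 133.8) = 0.32, ρ = 0.57.

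In patients, 1/(1 − R²) = 1.30 and 1.47, that is 30–47% more. After dividing by the 1.029 cost this is 26–43%.

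If extent were confined to the former 20–50% (M = 35, V = 30²/12 = 75, SD 8.7), R² would be 6.75/45.75 = 0.15 and 18.75/88.1 = 0.21, or 17–27% more patients. Other fraction distributions on the 20–75% range gave ρ from 0.34 to 0.84.

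*Model B: gain = the smaller of the affected area and an outgrowth unrelated to extent.* Mean outgrowth of 20 points (SD 8) gives ρ = 0.06, and 30 (SD 10) gives 0.25. As the ceiling is reached more often, ρ rises: 0.45 at 40 (SD 15) and 0.86 at 60 (SD 15).

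**Step 3: simulated power, 13 per arm, ANOVA v ANCOVA.**
- Model A, mean cleared fractions 0.30/0.40/0.55: 0.50–0.52 v 0.64–0.67 over separate runs.
- Model A, one arm 0.75 and two at 0.50 (Beta fractions with parameters summing to 4): 0.54 v 0.78. With no difference between arms, type I error was 0.053 v 0.052.
- Model B, arm means 12/16/22, SD 8: 0.79 v 0.77 and, in a second run, 0.78 v 0.77.
- Model B, arm means 15/20/27, SD 10: 0.72 v 0.71 and, in a second run, 0.73 v 0.73.

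**Step 4: chance imbalance.** With uniform 20–75% extent and 13 per arm, the largest arm mean exceeds the smallest by about 7.3–7.5 points on average, and by more than about 12.5 in one trial in ten. Under Model A the slope of gain on extent is the mean cleared fraction, 0.3–0.5. A 7.3-point imbalance therefore shifts mean gain by 7.3 × 0.3 = 2.2 to 7.3 × 0.5 = 3.7 points, not by 7.3.

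No calculation was done for length.

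**The case against.** The strongest reply is that a ceiling on gain produces a correlation only if patients come near it. The month-6 criteria concern nail growing out, in millimetres from the proximal fold or as area with evidence of outward growth. If growth over six months is the limit, extent hardly matters and adjustment earns nothing. This stands: the article cannot settle which model applies, and the benefit is conditional.

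A reader might infer that the unadjusted comparison is biased, or that chance differences in extent pass in full into the regimen comparison. The article does not support either. Randomisation keeps the test valid, the type I error in Step 3 is about 5% both ways, and the ANOVA standard error already allows for chance imbalance.

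A reader might also infer that the main efficacy result is at risk. It is not. The efficacy endpoints in sections 2.5 and 2.6 are proportions compared by chi-square, and mean increase is not listed among them.

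Nor does the article show that randomisation was unstratified; it is silent, and a full protocol may say more. The uniform 20–75% distribution is doubtful too. Patients enrolled before the amendment could not exceed 50%, and the 3 mm proximal limit and the lunula exclusion restrict high involvement. Step 2 shows a smaller benefit for the narrower range.

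Finally, covariates are often left to an analysis plan, which is not shown here. But the article does fix the test family, and neither named test adjusts. The discretion clause is no substitute: in an open-label trial, a choice of covariates left open can be made after results are seen.

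**Conclusion.** The point holds as a nearly free improvement of moderate to minor severity, not as an error. The plan leaves recorded baseline information out of the continuous comparison. In area, using it would be worth roughly 30–47% more patients (26–43% net of the cost of estimating the slope) if gain is a share of the affected area and extent is spread over 20–75%. It would be worth nothing, at a cost of about 1–2 points of power, if outgrowth unrelated to extent limits the gain. Break-even is a correlation of about 0.17. The possible loss is larger than the possible cost, which favours adjusting, but the article does not establish that baseline extent strongly predicts gain. For length the same reasoning is plausible but unquantified.

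**What to change.** In section 2.8, prespecify ANCOVA of month-6 clear-nail area and of month-6 clear-nail length, with regimen and the matching baseline measure as terms: affected area for area, distance from the proximal nail fold for length. Report adjusted differences between regimens with 95% confidence intervals. Use robust or bootstrap standard errors, because if regimens clear different shares of the affected area, the slopes differ by arm and the variance grows with extent, so a common-slope model is only approximate. Name a rank or permutation version for clearly non-normal residuals, in place of Kruskal–Wallis. Keep the unadjusted means as description.

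The cost is a sentence or two of text and one residual degree of freedom (35 instead of 36). No new data or visits are needed. The choice should be fixed before outcomes are examined by regimen; the article expects interim data in December 2024.

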### Treatment procedures

2.3

At enrolment, one affected hallux will be designated as the treatment target; up to 3 additional ‘non‐target’ toenails may also receive treatment. Prior to treatment, all visual and photographic assessments will be performed, in addition to sampling for mycology testing, as per the study schedule (Figure 1).

During each treatment session, toenails will be prepared by the clinician. Nails will be soaked in warm water for a minimum of 5 min to aid hydration and microwave energy absorption thereby generating heat in the nail plate and nail bed; then they will be cleaned with an antiseptic solution and allowed to dry. Microwave energy will be applied locally at a pre‐specified dose of 7–9 W for up to 3 s (i.e., one “burst”); treatment may be initiated at 9 W for up to 3 s with further adjustments of power and time settings depending on patient tolerability. Up to 5 additional bursts, spaced approximately 5‐s apart and subject to patient tolerability, may be administered in the same location and then repeated at a new location to ensure complete coverage of the nail surface. The affected nail area for treatment is chosen by the clinician administering the microwave energy and is concentrated on the proximal margin of discolouration and then distally as needed. The dose, duration and number of repetitions from each session will be recorded.

Investigators will follow the operation manual of the microwave device (Swift^®^ System, Emblation Ltd.). A new disposable tip will be fitted to the applicator probe used during each treatment session of up to 15 min from the first delivery of microwave energy. Ambient operating temperature should be between 10 and 30°C.

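### Clear-nail gain is to be related to treatments, energy and visits actually received, with no cut-off before retreatment of non-responders and no adjustment for disease extent, so the dose-response can be spurious or reversed

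*Protocol article*

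**What the plan says.** Section 2.8 (Data analysis) lists the mean increase in clear nail as one analysis. It then adds, as separate items, the "mean increase in clear nail as a function of the number of treatments and energy dose administered" and the "mean increase in clear nail as a function of the number of visits attended". All of these "will be analysed using ANOVA or the Kruskal"–Wallis test, and p "< 0.05 will be considered statistically significant". No time point, covariate or rule for retreated patients is attached. Any further correction is left to the statistician's judgement.

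Section 2.2 (Study intervention) randomises the schedule: "Group A will undergo nine treatment sessions", "Group B will undergo 7 treatment sessions", and Group C has 12. Non-responders on the clear-nail endpoint at month 6 or month 9 "will be given the option to undergo retreatment once per month for 3 months up to month 9 or month 12, respectively". Those who decline come back only at months 9 and 12. Section 2.4 follows everyone to month 12.

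Section 2.3 (Treatment procedures) has bursts given at one spot and "then repeated at a new location to ensure complete coverage of the nail surface". The clinician chooses the area to treat, and power and time are adjusted to tolerability. Table 1 admits nails with 20% to 75% involvement.

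**The concern.** The exposures named in 2.8 are what patients received, not what they were assigned. Two mechanisms can then produce an association without any treatment effect.

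- **Sessions and visits after month 6.** Poor clear-nail gain is what entitles a patient to more sessions and more visits. Relating clear-nail gain to those counts puts the outcome on both sides and pushes the association downward.
- **Energy at any time point.** If energy dose means the total delivered, a larger affected area can need more positions and so more energy. A larger affected area also leaves more area that can clear. This pushes the association with cleared area upward. Poor tolerability lowers energy and may itself be related to outcome.

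One-way ANOVA and Kruskal–Wallis compare groups. They take no covariate in that form, and a continuous exposure such as energy must be cut into categories first.

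The secondary objective is to find an optimal dosing frequency for a pivotal trial. A significant result of the wrong sign on session count, or a significant energy result that reflects disease extent, could mislead that choice.

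**Working it through.** The article gives no dose-response or power figure to reproduce; it states that no sample size calculation was done. The check therefore rebuilds the session counts and then simulates the described analysis with no true effect.

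**1. Session counts (section 2.2; a month taken as 28 days)**

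- A: days 0, 7, 14, 21, 28, 56, 84, 112, 140 = 9 sessions.
- B: days 0, 14, 28, 56, 84, 112, 140 = 7 sessions.
- C: every 14 days from 0 to 154 = 12 sessions.

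All fall before the month-6 visit at day 168. Retreatment adds 3 sessions, or 6 if both periods may be used, which the text does not settle:

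- A: 9 + 3 = 12 to 9 + 6 = 15.
- B: 7 + 3 = 10 to 7 + 6 = 13.
- C: 12 + 3 = 15 to 12 + 6 = 18.

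A Group B non-responder (up to 13) can thus exceed a Group C responder (12). The total no longer represents the randomised regimen.

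**2. Sessions, no true dose effect**

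Assumptions, none from the documents:

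- Month-6 gain is normal with SD 3 mm and mean 6 + 3·z(p), where p is the month-6 response rate at the 6 mm threshold.
- Each later period adds a change of SD 1 mm unrelated to treatment.
- A patient below 6 mm at month 6, and again at month 9, accepts 3 sessions with the stated uptake.
- 1,000 trials per case.

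Kruskal–Wallis on month-12 gain by total sessions, percentage of trials with p < 0.05 (45 planned / 39 enrolled):

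| Response rate | Uptake 30% | Uptake 60% | Uptake 100% |
|---|---|---|---|
| 20% | 12 / 10 | 39 / 31 | 96 / 94 |
| 40% | 31 / 22 | 80 / 71 | 100 / 100 |
| 60% | 40 / 32 | 91 / 80 | 100 / 100 |

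The mean Spearman correlation ran from −0.16 to −0.68.

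With a true benefit of 0.3 or 0.5 mm per planned session up to month 6 (45 patients, 40% response, 60% uptake), the month-12 slope was −0.36 or −0.31 mm per session. The month-6 slope by arm was 0.31 or 0.50, so the sign is reversed only in the later analysis.

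**3. The same model at month 6, by arm**

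Mean correlation was about 0, and Kruskal–Wallis was significant in 3% to 6% of trials, close to the nominal 5%.

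**4. Energy, no true energy effect**

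A full burst delivers 7 × 3 = 21 J to 9 × 3 = 27 J. Extent varies 75/20 = 3.75-fold. Assumptions:

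- Extent is uniform on 20% to 75%.
- Energy = sessions × extent × lognormal variation (log-SD 0.2 or 0.4).
- Cleared area = fraction × extent, with the fraction (mean 0.4, SD 0.25, kept within 0 to 1) independent of energy.
- 45 patients, 2,000 trials.

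| Log-SD | Mean Spearman, energy v. cleared area | Kruskal–Wallis by energy tertile, p < 0.05 |
|---|---|---|
| 0.2 | +0.35 | 51% |
| 0.4 | +0.28 | 33% |

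With extent removed by analysing the fraction cleared, the correlation was about 0 and about 5% of trials were significant. In this model the expected cleared area given extent and energy is (mean fraction) × extent, with no energy term. A linear regression with extent as covariate therefore targets zero for energy, as it should.

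**The case against.** **The time point is not stated.** Every clear-nail gain endpoint in sections 2.5 and 2.6 sits at month 3 or month 6; months 9 and 12 carry only mycological and effective cure. If 2.8 means month 6, the planned count is the arm and a three-group test fits. An article may also leave such detail to the full protocol or analysis plan. This stands as a limit on the point. It does not remove it, because the article itself fixes received exposures, the test and the threshold, with no cut-off, in a study that records data to month 12.

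**Energy dose may not mean total energy.** Section 2.3 uses dose for the power setting in watts and records dose, duration and repetitions separately. It speaks of covering the nail surface in one sentence and of the affected area in another. On the power-setting reading only the tolerability concern remains. This stands, so the energy part is conditional.

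**A reader might infer that the dose-response must be spurious.** The documents do not support that. Month-6 analysis by arm is sound apart from missed sessions, and the later bias depends on unknown uptake. With 13 per arm, mean gain 5 mm, SD 3 mm and one retreatment round, uptake of 30% gave a mean correlation of −0.14 (13% of trials significant) and 50% gave −0.22 (28%). Two rounds at 80% uptake gave −0.54 (98%), which is near the ceiling and not a forecast.

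**A reader might also infer that sessions will look harmful and energy beneficial in the same data.** A joint simulation does not bear this out (13 per arm, 80% uptake, two rounds, nail assumed 15 × 15 mm, mean 45% of affected area cleared). At month 12, sessions gave −0.54 but energy only +0.06 (7% significant). At month 6, energy gave +0.37 (65%) but sessions 0.00 (5%).

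**Nor does the article say that this analysis selects the pivotal regimen.** The between-group comparisons address the dosing-frequency objective directly. This analysis is supporting evidence for it.

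**Conclusion.** The concern holds in a limited form.

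- **Sessions and visits:** any analysis using counts after month 6 is confounded by outcome, and can show a spurious or reversed dose-response. For session totals the simulated false-positive rate was 10% to 100% against a nominal 5%. That width reflects assumed response rates and uptake, so it shows direction and plausible range only. Visits share the mechanism but were not simulated. Up to month 6, planned sessions are unaffected.
- **Energy:** if total energy is meant, its relation with cleared area is biased upward by disease extent (simulated null rejection about 33% to 51%, assuming energy proportional to affected area). This is less certain for clear-nail length, which was not simulated.

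The wording should be changed, because the correction is cheap and the result may bear on the choice of dosing frequency.

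**What to change.** In section 2.8:

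1. Restrict these analyses to data up to day 168, before any retreatment.
2. For number of treatments, use the randomised regimen (7, 9 or 12 planned sessions) as the exposure.
3. Define energy dose. If it is total energy, keep it continuous in a regression with baseline affected area as covariate, and label the model observational and exploratory. The spread of cleared area is likely to grow with extent, so robust standard errors are advisable.
4. Drop the visits-attended analysis, or limit it to day 168 and call it descriptive.
5. Describe data from retreated patients after month 6 without a dose-response test.

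No new data are needed: affected area is measured at enrolment (section 2.1), and dose, duration and repetitions are recorded at each session (section 2.3). Energy per unit of treated area is not a safe substitute, because treated area is not among the items listed as recorded.

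The cost is that the number-of-treatments analysis becomes a contrast of arms, and retreatment data after month 6 are only described. The tolerability influence on energy also remains, hence the exploratory label.
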